**ED visit**																												
	Screening form			RA^d^		N/A^e^		✓		✓																		
	Case report (acute signs and symptoms)			RA and MD^f^		5 RA and 5 MD		✓		✓																		
	Balance (balance error scoring system)			CP^g^		5-10		✓		✓																		
**Outcomes**																												
	**Psychological**																											
		Self-Efficacy Questionnaire for Children	C		2-5								✓		✓										✓		✓	
		Connor-Davidson Resilience Scale	C		2-5								✓		✓										✓		✓	
		Generalized Anxiety Disorder 7-item scale	C		2-5		✓								✓										✓		✓	
		Center for Epidemiologic Studies Depression Scale for Children	C		2-5		✓								✓										✓		✓	
		Child and Adolescent Mindfulness Scale	C		2-5		✓								✓										✓		✓	
		Credibility Expectancy Questionnaire	C		5														✓									
		Client Satisfaction Questionnaire	CP		5																				✓			
	**Postconcussive symptoms (secondary)**																											
		Health and Behavior Inventory	C		5-10		✓		✓												✓				✓		✓	
		Post-Concussion Symptom Inventory	C		5		✓		✓												✓				✓		✓	
	**Functional impairments (secondary)**																											
		Quality of Life (PedsQL^h^)^i^ scale	C		5-10		✓								✓										✓		✓	
		PedsQL Fatigue scale	N/A		N/A																				✓		✓	
	**Neurophysiological measures (subset of 60 participants)**					45																						
		Arterial spin labeling	C														✓								✓			
		Resting-state fMRI^j^	C														✓								✓			
		MRS^k^	C														✓								✓			
**Cognitive measures**																												
		NIH^l^ Toolbox	C		25																				✓			
		App Measurements	N/A		N/A						✓																	
		Godin-Shephard Leisure-Time Physical Activity Questionnaires	C		5								✓		✓						✓				✓		✓	
		Puberty Questionnaire	C		5		✓								✓													

^a^CHEO ED: Children’s Hospital of Eastern Ontario emergency department.

^b^360cc: 360 Concussion Care.

^c^When accessing the app.

^d^RA: research assistant.

^e^N/A: not applicable.

^f^MD: treated ED physician.

^g^CP: concussed child and parent or guardian.

^h^PedsQL: Pediatric Quality of Life Inventory.

^i^Outcome measure.

^j^fMRI: functional magnetic resonance imaging.

^k^MRS: magnetic resonance spectroscopy.

^l^NIH: National Institutes of Health.

#### Secondary Outcomes

##### Treatment Expectancy

*Treatment expectancy* will be assessed with the Credibility and Expectancy Questionnaire (questions 4 to 6) [51]. Expectancy will be considered good if the participants score above the midpoint on questions 4 to 6. Expectancy will be assessed at 1 week after the enrollment.

##### Intervention Satisfaction

*Intervention satisfaction* will be assessed with the modified version of the Client Satisfaction Questionnaire [52]. This is a validated, reliable, 8-item questionnaire used to measure client satisfaction with a particular program or service. In this case, the questionnaire has been modified to assess participant satisfaction with the digital intervention. The intervention will be deemed satisfactory if >70% of the participants score above the midpoint on the questionnaire [52]. Intervention satisfaction will be assessed at 4 weeks after the enrollment (end of the intervention).

##### Quality of Life

*QoL* will be measured using the Pediatric Quality of Life Inventory (PedsQL; version 4.0) [53,54]. The PedsQL is a reliable and valid measure of QoL in healthy children and adolescents and in those with acute or chronic health conditions [55]. It is a 23-item, 5-point Likert scale questionnaire yielding a total score (0-92) and 4 domain scores: physical, emotional, social, and school. QoL will be collected in the ED (for CHEO participants) or on day 1 (for 360cc participants) and at the 4- and 8-week follow-ups.

##### Fatigue

*Fatigue* will be measured using the Multidimensional Fatigue Scale PedsQL. This 18-item, 5-point Likert scale assessment comprises 3 scales: the General Fatigue Scale (6 items), Sleep-Rest Fatigue Scale (6 items), and Cognitive Fatigue Scale (6 items). The PedsQL Multidimensional Fatigue Scale has demonstrated excellent internal consistency, reliability, and validity [56-58]. The assessment will be collected in the ED (for CHEO participants) or on day 1 (for 360cc participants) and at the 4- and 8-week follow-ups.

##### Symptom Burden

*Symptom burden* will be measured in the ED or at 360cc (both retrospective and postinjury acute symptoms) and at 1, 2, 4, and 8 weeks after enrollment using the Health and Behavior Inventory (HBI) [3]. The HBI is a 20-item self-report questionnaire that uses a 4-point Likert scale, with a total range 0-60. It provides scores for cognitive and somatic symptom scales. Emotional symptoms and sleep disturbances will be assessed using the Post-Concussion Symptom Inventory (PCSI) [59-61]. The PCSI [59,60] is a validated, reliable, comprehensive, and self-administered instrument [59-61]. For the purpose of this study, the emotional and sleep domains of the PCSI adolescent scale version (20-item, 7-point Likert scale) will be used. The domains will be assessed in the ED or at 360cc and at 2, 4, and 8 weeks after enrollment.

##### Self-Efficacy

*Self-efficacy* will be measured using the Self-Efficacy Questionnaire for Children (SEQ-C). Self-efficacy is the individual’s perceived and personal competence in their abilities to handle a situation. Self-efficacy reflects one’s confidence in the ability to exert control over one’s motivation, behavior, and social environment. Previous studies have demonstrated that at 12 weeks after the injury, children with a concussion lack confidence during physical activities at 12 weeks after a concussion as compared with that before the injury [62]. The SEQ-C is a valid and reliable assessment tool. It is a 24-item, 5-point Likert scale yielding a sum score (0-120) and emotional, social, and academic self-efficacy subscores [63]. The SEQ-C will be administered on day 1 and at 4 and 8 weeks after enrollment.

##### Attention, Working Memory, and Executive Function

Attention, working memory, and executive function will be assessed using the National Institutes of Health (NIH) Toolbox Cognitive Battery [64]. The NIH Toolbox is a validated and reliable computerized battery designed to measure executive function, attention, episodic memory, language, processing speed, working memory, and fluid cognition. Previous studies have demonstrated lower working memory, attention, and executive functioning scores after injury in pediatric samples with concussion [65-68]. Moreover, mindfulness has been shown to improve attention, working memory, and executive functioning [26,69,70]. The NIH Toolbox will be administered at the 4-week follow-up.

##### Resiliency

*Resiliency* will be measured using the Connor-Davidson Resilience Scale-10 (CD-RISC-10) [71]. The CD-RISC-10 is a 10-item questionnaire, scored on a 5-point Likert scale, that assesses an individual’s perception of hardiness or perceived stress. Resiliency is defined as the ability to harbor interpersonal qualities, such as positive acceptance, to adapt or thrive in the face of adversity [71]. Previous research has shown that MBI increases resiliency in youth [13]. The CD-RISC-10 has been validated in an adolescent population with a concussion [72] and will be administered on day 1 and at 4 and 8 weeks after enrollment.

##### Anxiety and Depression

*Anxiety* and *depression* (mood) are frequently reported symptoms in pediatric concussion [73-75]. *Anxiety* will be measured using the Generalized Anxiety Disorder 7-item scale [73]. The Generalized Anxiety Disorder-7 is a validated, reliable, and sensitive to treatment-related changes tool that assesses anxiety symptoms in youth [76]. It is a 7-item, 3-point Likert scale that provides a sum score (0 to 21) of general anxiety symptoms. It will be administered in the ED (for CHEO participants) or on day 1 (for 360cc participants), capturing preinjury anxiety, and at 4- and 8-week intervals after enrollment to assess postenrollment anxiety.

*Depression* symptoms will be measured using the validated and reliable Center for Epidemiologic Studies Depression Scale for Children [74,75]. It is a 10-item, 4-point Likert scale that provides a total score (0-30). The Center for Epidemiologic Studies Depression Scale for Children will be administered in the ED (for CHEO participants) or on day 1 (for 360cc participants), capturing preinjury mood, and at 4- and 8-week intervals after enrollment to assess postenrollment mood.

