**Methods:**

This study is a double-blind Health Canada–regulated trial. A total of 70 participants will be enrolled within 7 days of concussion and randomly assigned to receive the 4-week DTx MBI (experimental group) or comparator intervention. Feasibility will be assessed based on the recruitment rate, treatment adherence to both interventions, and retention. All outcome measures will be evaluated before the intervention (within 7 days after injury) and at 1, 2, and 4 weeks after the injury. A subset of 60 participants will undergo magnetic resonance imaging within 72 hours and at 4 weeks after recruitment to identify the neurophysiological mechanisms underlying the potential benefits from MBI training in adolescents following a concussion.

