##### Mindfulness

*Mindfulness* will be assessed using the validated Child and Adolescent Mindfulness Measure [77,78]. It is a 10-item, 5-point Likert scale. It will be administered in the ED (for CHEO participants) or on day 1 (for 360cc participants), capturing preintervention mindfulness, and at 4- and 8-week intervals after enrollment to assess postenrollment mindfulness.

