#### Secondary Outcomes

Mean and SDs will be computed for each collected measure. Pre-post correlations will be generated to assess preliminary evidence of *efficacy signal* for QoL, fatigue, symptoms, resiliency, self-efficacy, cognition, anxiety, depression, and mindfulness.

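### Anxiety and depression have only a preinjury baseline, so their pre-post correlation or change cannot be read as an intervention effect

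*Protocol article*

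**What the plan says.** The protocol article, under Anxiety and Depression, gives the GAD-7 once at entry (in the emergency department at the hospital site, on day 1 at the concussion clinic), "capturing preinjury anxiety, and at 4- and 8-week intervals after enrollment to assess postenrollment anxiety". The depression scale follows the same schedule, "capturing preinjury mood, and at 4- and 8-week intervals after enrollment to assess postenrollment mood". Table 3 agrees: one entry administration per site for each scale, then weeks 4 and 8, with nothing between.

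Elsewhere the article keeps the preinjury and current states apart. Under Symptom Burden the Health and Behavior Inventory (HBI) is collected at entry for "both retrospective and postinjury acute symptoms". Under Mindfulness the entry measure is described as "capturing preintervention mindfulness, and at 4- and 8-week intervals after enrollment to assess postenrollment mindfulness".

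The Secondary Outcomes part of Statistical Analysis plans means and SDs for every measure, then states: "Pre-post correlations will be generated to assess preliminary evidence of" an efficacy signal "for QoL, fatigue, symptoms, resiliency, self-efficacy, cognition, anxiety, depression, and mindfulness". Anxiety and depression are on that list. The abstract says: "All outcome measures will be evaluated before the intervention (within 7 days after injury) and at 1, 2, and 4 weeks after the injury".

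**The concern.** A pre-post analysis takes its meaning from what lies between the two measurements. For anxiety and depression, the first value describes the adolescent before the concussion and the second describes the same adolescent four weeks into the study. The article itself gives the frequency of anxiety and low mood after pediatric concussion as the reason for measuring them, so the injury can be expected to move these scores.

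Two uses are at stake. First, within-arm pre-post figures may be read as preliminary evidence that the app does or does not help. Second, the Secondary Research Objectives include estimates for the sample size of a later multicenter trial. A correlation or change SD from preinjury to week 4 is not the quantity needed if that trial adjusts for, or measures change from, a post-injury, pre-treatment score.

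**Working it through.** The document states no figure that depends on this point, so there is none to reproduce. The check compares the entry measures and then uses simple algebra.

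**1. What each entry value describes**

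| Measure | State captured at entry | Current state before treatment available? |
|---|---|---|
| HBI | retrospective and acute post-injury | yes |
| Mindfulness | before the intervention | yes |
| GAD-7 | preinjury | no |
| Depression scale | preinjury | no |

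**2. What a within-arm change contains**

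Measured against the preinjury state, let *a* be the concussion effect at entry, *c* the concussion effect still present at week 4, and *t* the app effect (negative = benefit).

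- Preinjury to week 4: mindfulness arm *c + t*; sham arm *c*; difference *t*.
- Post-injury entry to week 4: mindfulness arm *(c − a) + t*; sham arm *c − a*; difference *t*.

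The documents give none of these quantities. With assumed values in SD units, from a preinjury baseline:

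| *c* | *t* | Mindfulness arm | Sham arm | Difference |
|---|---|---|---|---|
| 0 | −0.3 | −0.3 | 0 | −0.3 |
| 0.3 | −0.3 | 0.0 | +0.3 | −0.3 |
| 0.6 | −0.3 | +0.3 | +0.6 | −0.3 |
| 0.6 | 0 | +0.6 | +0.6 | 0 |

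The same app effect looks like benefit, no effect or harm within the arm, depending only on *c*. The between-arm difference is *t* in every row.

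**3. Whether a post-injury baseline would rescue pre-post change**

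Take assumed GAD-7 means: preinjury 4, acute 8, week 4 of 5 (mindfulness) and 6 (sham).

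- From preinjury: 5 − 4 = +1 and 6 − 4 = +2; difference −1.
- From acute: 5 − 8 = −3 and 6 − 8 = −2; difference −1.

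With the acute baseline, 2 of the 3 points of improvement also occur under sham. The injury has left the interval but natural recovery remains in it. Only the sham arm removes either.

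**4. What a correlation contains**

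A correlation does not change when a constant is added to all week-4 scores, so it carries neither *c* nor *t* as a mean shift. It shows how well one score predicts the other. Here that is preinjury status predicting week 4, which is useful for planning a trial that adjusts for preinjury status but is not evidence of efficacy.

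**5. Precision of the adjusted week-4 comparison**

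With covariate–outcome correlation ρ, residual variance is 1 − ρ² of the unadjusted variance:

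- ρ = 0.3: 1 − 0.09 = 0.91
- ρ = 0.5: 1 − 0.25 = 0.75
- ρ = 0.6: 1 − 0.36 = 0.64

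If a post-injury score had ρ = 0.6, the residual variance relative to the preinjury score would be:

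- preinjury ρ = 0.3: 0.64 / 0.91 = 0.70, about 30% lower
- preinjury ρ = 0.5: 0.64 / 0.75 = 0.85, about 15% lower
- preinjury ρ = 0.6: no difference

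All of these correlations are assumed.

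**The case against.** The strongest reply is that this is a randomised trial, so the comparison that matters is between arms. Both arms share the same preinjury baseline and the same injury, and that comparison is unbiased. This is correct, and a reader should not infer that the randomised week-4 result is compromised. It does not settle the matter, because the plan names pre-post correlations, not that comparison, as the source of the signal for these outcomes. The Discussion mentions effect sizes against the control group only for quality of life and symptoms.

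Other parts of the reply also stand:

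- A reader might infer that the planned analysis would show both arms worsening. The plan names means, SDs and correlations but no change score, so apparent worsening would arise only if someone subtracted the means.
- Preinjury status is worth measuring. The Background cites preexisting anxiety and mood concerns as lasting predictors of persistent symptoms, so it is a sensible covariate. It cannot be assumed that a post-injury score would predict week 4 better.
- Emotional state after injury is not wholly unmeasured. The Post-Concussion Symptom Inventory emotional domain is collected at entry, and the app records mood and stress. These are different instruments and do not supply a GAD-7 or depression-scale baseline.
- The Discussion says the later trial will target quality of life and symptom burden, and no text fixes its baseline. This limits the sample-size consequence to any use of anxiety and depression there.
- The abstract is not contradicted on timing, since both forms are completed before the intervention. It only leaves unsaid that these two describe an earlier state.

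**Conclusion.** The point holds for the pre-post reading of two secondary outcomes. The GAD-7 and the depression scale have no post-injury, pre-treatment value, yet the plan takes their efficacy signal from a pre-post analysis whose interval spans the concussion. Within-arm change or correlation therefore cannot be read as an intervention effect, and it does not describe the interval from a post-injury baseline to week 4 for a future trial.

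The size of the distortion cannot be computed from the document. In the assumed cases, a residual concussion effect of 0.3 SD hides a benefit of 0.3 SD, and one of 0.6 SD turns it into apparent harm.

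The consequence is limited. The randomised week-4 difference is unbiased and none of the five progression criteria depends on these scales. A reader might also infer that a post-injury baseline would make pre-post change a valid signal, or that about 30% of residual variance is being lost. Neither is supported: natural recovery would still be in the change, and the precision gain ranges from none to about 30% over the assumed correlations.

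**What to change.** 1. In the Secondary Outcomes part of Statistical Analysis, define the anxiety and depression signal as the week-4 difference between arms with its confidence interval, adjusted for the preinjury score as a covariate. State that preinjury-to-week-4 change or correlation will not be presented as efficacy. If the correlation is reported for planning, label it as preinjury to week 4. This uses data already scheduled and costs only wording.
2. In the abstract's Methods, add that the entry anxiety and depression scales describe the preinjury state.
3. Optionally, for participants still to be enrolled, add a current-state GAD-7 and depression scale, completed before allocation is obtained. Table 3 puts each at 2 to 5 minutes, so 4 to 10 minutes per participant once, plus an amendment. Recruitment began in October 2022 and data collection was expected to end by September 2024, so only part of the sample would have the new measure. Change from it would still include natural recovery and must be compared with the sham arm.

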##### Mindfulness

*Mindfulness* will be assessed using the validated Child and Adolescent Mindfulness Measure [77,78]. It is a 10-item, 5-point Likert scale. It will be administered in the ED (for CHEO participants) or on day 1 (for 360cc participants), capturing preintervention mindfulness, and at 4- and 8-week intervals after enrollment to assess postenrollment mindfulness.

##### Safety

*Safety* of the MBI will be determined by capturing and monitoring the worsening of symptoms and adverse events. Adverse events will be defined as an unscheduled visit to the ED or primary medical provider because of exacerbation of symptoms during or within 30 minutes after using the app. The participant will be asked about any possible adverse events at the 1-, 2-, 4-, and 8-week follow-ups.

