### Study Setting

The study will be conducted at the Children’s Hospital of Eastern Ontario (CHEO) and the 360 Concussion Care (360cc) clinic, a tertiary health care concussion clinic. The neuroimaging component of the study will be completed at the Royal Ottawa Mental Health Centre’s Brain Imaging Centre on a 3-Tesla Siemens magnetic resonance-positron emission tomography system with a 32-channel head coil (Siemens Biograph mMR, Siemens).

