### Eligibility Criteria

#### Inclusion Criteria

Adolescents presenting to either CHEO’s emergency department (ED) or 360cc after sustaining a direct or indirect mild traumatic brain injury (TBI) will be eligible to participate in this study if they (1) are aged 12 to <18 years; (2) have a diagnosed concussion (by a physician), (3) presented to the ED or 360cc within 7 days of TBI; (4) have a score >4 on the Predicting and Preventing Post-Concussive Problems in Pediatrics (5P) clinical risk score, a prediction rule to identify those at risk of poorer outcomes at 4 weeks postinjury [2]; and (5) are proficient in English [38]. To increase the probability of including adolescents with a true concussion, the adapted version of the American Congress of Rehabilitation Medicine [39] framework will be used [40]. Those with either 1 *highest level of certainty* symptom (dazed, confused, or trouble thinking within minutes after injury, difficulty remembering what happened just before or minutes after injury, and loss of consciousness) or 2 *higher level of certainty* symptoms (nausea or vomiting, headache, dizziness, clumsy or balance problems, blurred or double or change in vision, difficulty concentrating, and sensitivity to light or noise) immediately or within 1 hour of injury will be included.

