#### Standard of Care

All the participants will receive standard of care [46] instructions pamphlet provided by RAs in the ED or at 360cc. The standard of care indicates that the patient refrains from physical and cognitive activities for 24 to 48 hours after injury. After the rest period, it is recommended that low-to-moderate levels of physical and cognitive activity be gradually started, including screen time. The activities should be performed at a level that does not result in the recurrence or exacerbation of symptoms. Adolescents must refrain from any activities that increase the risk of reinjury (eg, contact sports or anything with risk of falls) until fully asymptomatic and cleared by their primary care or other medical providers.

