#### Potential Harms

The safety outcomes include (1) severe worsening of symptoms identified on HBI reliable changes or (2) any symptoms requiring an unscheduled visit to the ED or primary care provider. If concussion symptoms worsen during the treatment to the degree that the participant requires an unscheduled visit to the ED or primary care provider, then symptoms will be considered as a possible adverse event. Symptoms could develop into an adverse event if they become unbearable and the patient needs immediate medical attention. Patients will report possible adverse events through REDCap reports, and their responses will be monitored by RAs. In the case of a possible adverse event, defined as the *worsening of symptoms requiring an unscheduled visit to the ED or primary care provider*, site investigators will be notified to determine if the event is linked to the treatment. If linked, the event will be monitored and the CHEO Research Ethics Board and DSMB will be notified.

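### Read literally, the adverse-event definition leaves out unscheduled visits to 360cc or another specialist, so the safety count may miss some events

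*Protocol article*

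**What the plan says.** The Safety section (under Secondary Outcomes) states: "Adverse events will be defined as an unscheduled visit to the ED or primary medical provider because of exacerbation of symptoms". It adds a time limit, "during or within 30 minutes after using the app". On ascertainment it states: "The participant will be asked about any possible adverse events at the 1-, 2-, 4-, and 8-week follow-ups".

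Potential Harms (under Data Safety and Monitoring) gives two safety outcomes: "severe worsening of symptoms identified on HBI reliable changes" or "any symptoms requiring an unscheduled visit to the ED or primary care provider". It repeats the pairing of ED and primary care twice more. The first is in the sentence on worsening during treatment. The second is in the definition of a possible adverse event, which leads to the site investigators being notified and judging whether the event is linked to treatment. If they find a link, the ethics board and the DSMB are told. This section has no 30-minute limit.

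Study Setting lists, as the second site, "the 360 Concussion Care (360cc) clinic, a tertiary health care concussion clinic". The inclusion criteria admit adolescents who "presented to the ED or 360cc within 7 days of TBI". Standard of Care has patients "cleared by their primary care or other medical providers", so the article itself separates primary care from other providers. Secondary Research Objectives compares the arms on the total number of adverse events.

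**The concern.** The definition sorts events by where the participant sought care. A participant recruited at 360cc whose symptoms flare could plausibly return to that clinic. The inclusion criteria treat it as a place where patients present soon after injury, and Data Collection Methods refers to its staff as part of the circle of care. On the literal wording that visit is not an adverse event, while the same flare seen in the ED could be. The same applies to a visit to any other specialist or mental-health service, whichever site recruited the participant.

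Two things depend on the definition: the between-arm comparison of total adverse events, which is a stated secondary objective, and the start of investigator causality review. In a trial of 70 adolescents the number of events is likely to be small, so a rule that turns on the type of clinic is an avoidable weakness.

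**Working it through.** The document states no expected adverse-event count, so there is no figure to reproduce. The check is a comparison of the passages.

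1. **Places of care that qualify.** Safety: ED or primary medical provider. Potential Harms, three times: ED or primary care provider. No statement of the visit rule names 360cc or refers to other providers.
2. **Status of 360cc.** Study Setting calls it tertiary. It is a recruiting site, and elsewhere the article pairs it with the ED (inclusion criteria, Standard of Care, Symptom Burden, Data Collection Methods). The visit rule keeps the ED and drops 360cc.
3. **Could primary provider be read to include 360cc?** Standard of Care distinguishes primary care from other medical providers, which points against it. The Safety section's slightly different term, primary medical provider, leaves some room for staff to interpret, but a definition should not depend on that.
4. **Other routes by which harm is captured.**
   - HBI reliable change needs no visit. The HBI is given at scheduled follow-ups and scores cognitive and somatic symptoms, while emotional and sleep symptoms are taken from the PCSI (Symptom Burden). A transient or mainly emotional flare could be missed. Potential Harms attaches no investigator causality review to this outcome.
   - Potential Harms also says that symptoms could become an adverse event if they are unbearable and need urgent attention, with no place of care given. The same section then defines a possible adverse event by an ED or primary care visit, so the status of a 360cc visit is at best unclear.
   - The DSMB may react to trends of increased symptoms (Data Safety Monitoring Board).
5. **Time window.** Safety requires the flare to be tied to app use within 30 minutes. Potential Harms refers only to worsening during treatment. A visit can meet one definition and fail the other, whatever the type of provider.
6. **Size.** Let s be the share of otherwise qualifying unscheduled visits that go to 360cc or another unlisted provider. A literal count captures 1 − s of them. The document gives no value for s. With s = 0 the capture is 1 − 0 = 1 and nothing is lost; with a larger s the loss equals s.
7. **Effect between arms.** The same rule applies in both arms and allocation is randomized 1:1, so the expected capture is the same unless place of care differs by arm, which nothing in the document suggests. Randomization is stratified by sex only, so the 360cc share may differ between arms by chance. If that share differs by d, a fraction m of events at 360cc is missed, event rates are equal by site and no such visits are missed for CHEO participants, capture differs by d × m. As an illustration with assumed values, d = 0.10 and m = 0.50 give 0.10 × 0.50 = 0.05, or 5 percentage points.

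**The case against.** The strongest reply is that the article shows no lost events. It does not say that 360cc takes unscheduled visits, or that staff would refuse to count one. Every participant is asked about possible adverse events at each follow-up, and harm is also captured by HBI reliable change, the urgent-attention sentence and DSMB review of symptom trends. Safety is not among the progression criteria in Table 2. The article is condensed: the REDCap question is not shown, and the DSMB and steering committee are to set safety outcomes before the start. On this view the contradiction over the 30-minute window is the larger defect.

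Much of this stands, and it limits how far the point goes. It does not remove the point, because the provider list is stated four times and is not a detail left to another document. Asking everyone does not help if the answer is then classified by the narrow list.

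A reader might infer more, namely that harm is under-counted at 360cc by a definite amount. Assuming that 20% to 50% of participants come from 360cc and that 30% to 70% of their visits go to that clinic or another specialist gives 0.2 × 0.3 = 6% to 0.5 × 0.7 = 35% of all events missed. The document supports neither input. The calculation also sets specialist visits by CHEO participants to zero, although the rule excludes those too. A reader might also infer a biased arm comparison, but a chance difference in site mix is noise and not systematic bias.

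**Conclusion.** The point holds as a gap in a stated rule. On a literal reading, an unscheduled visit for worsening symptoms to 360cc or another specialist falls outside the visit-based definition in both sections. The adverse-event total and the trigger for investigator review may therefore miss it. This rests on taking the provider list at its word and on a tertiary clinic not being a primary provider, which Study Setting and Standard of Care support.

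The size cannot be determined from the document and may be near zero, the other safety provisions close part of the gap, and no systematic bias between arms is shown. This is an inexpensive improvement to safety capture; it does not threaten the primary feasibility objective.

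**What to change.** Use one adverse-event definition in Safety and in Potential Harms. It should cover an unscheduled visit to any health care provider for worsening symptoms and expressly include 360cc and other specialist or mental-health services. Record the type of provider and tabulate events by site and arm.

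In the same edit, reconcile the 30-minute window after app use, which stands in Safety but not in Potential Harms, so that both sections apply the same time rule.

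The cost is a wording change in two sections and, if the REDCap adverse-event question does not already record it, a provider-type response. The downside is that the reported event count may rise. Recording provider type lets the narrower count be shown alongside the wider one.
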